### Procedure

2.4

Once a patient has consented to participate, a standardized baseline patient assessment will be performed, including the following:•V/Q SPECT/CT imaging. Ventilation imaging will be performed using either ^81m^krypton gas or ^99m^Tc-technegas (Cyclomedica), an ultrafine particle that exhibits near-optimal distribution properties. These 2 ventilation agents allow for optimal ventilation SPECT acquisition [31,32]. V/Q SPECT/CT images should not be used for patients’ management.•Collection of other potential predictor variables for VTE recurrence:-Demographic characteristics and risk factors for VTE.-Lab tests including D-dimer testing, drawn prior to discontinuation of OAT to mimic actual practice.-Lower limb compression ultrasonography if the patient had an associated DVT.•Functional evaluation:-Dyspnea index using Modified Medical Research Council (MMRC) scale and New York Heart Association (NYHA) score.-Quality of life index using Pulmonary Embolism (PEmb)-Qol questionnaire.-Cardiac ultrasound in case of residual dyspnea or if the V/Q SPECT/CT demonstrates RPVO.

Patients will be included in the study the day of anticoagulation discontinuation and will be followed up in clinic or contacted by telephone every 6 months up to 2 years. Patients will be educated about the signs and symptoms of recurrent VTE and given emergency contact numbers and instructions if these signs were to arise in follow-up. In case of suspected PE recurrence, the diagnostic and therapeutic management will be left at the discretion of treating physician according to the availability of imaging modalities. When a V/Q SPECT/CT scan is performed, recurrent PE will be diagnosed is there is 1 segmental or 2 subsegmental new mismatched perfusion defects [33,34]. The study design is presented in Figure.

**Figure fig1:**
[figure not shown]
Study design. PE, pulmonary embolism; Pemb-QoL, pulmonary embolism quality of life; RPVO, residual pulmonary vascular obstruction; V/Q SPECT, ventilation/perfusion single photon emission computed tomography; VTE, venous thromboembolism.

### Outcomes

2.5

The primary outcome is symptomatic recurrent VTE, including objectively confirmed nonfatal symptomatic PE or proximal DVT, or fatal PE during a 24-month follow-up after inclusion in the study [35]. All outcomes will be adjudicated blindly by an independent central Clinical Events Committee.

Secondary outcomes include following:•Symptomatic recurrent VTE during a 3-month follow-up period in patients with suspicion of PE recurrence left untreated based on a negative V/Q SPECT/CT scan. All suspicion of PE recurrence will be adjudicated blindly by an independent central Clinical Events Committee.•Dyspnea index assessed using MMRC scale.•Quality of life assessed using Pulmonary Embolism (PEmb)-Qol questionnaire.•Chronic thromboembolic pulmonary hypertension defined according to the European guidelines [36].•CTEPD will be defined as follows: dyspnea/functional limitation after at least 3 months of OAT, RPVO on lung scintigraphy, no evidence of pulmonary hypertension (mPAM < 25) at rest, and no other conditions that may contribute to symptoms.•Mortality of all causes.

### Statistical analysis

2.6

#### Variable analysis

2.6.1

Qualitative data will be presented as the number and the percentage of patients in each group (ie, patients with RPVO and patients with no RPVO). Quantitative data will be presented as mean and standard deviation, range, median, and IQR by group. Comparisons of qualitative variables between groups will be performed by a chi-square test or a Fisher’s exact test if required; comparison of quantitative data will be performed by the Student’s *t*-test or a nonparametric Wilcoxon test if required.

#### Analysis of the primary outcomeTime to occurrence of recurrent VTE (primary outcome) is described in the 2 groups by Kaplan–Meier curves

2.6.2

The subject’s time-to-event will be censored at 2 years (end of the follow-up period), anticoagulation for another reason than recurrent VTE or loss to follow-up, whichever occurs first. Kaplan–Meier curves will be compared using a log-rank test and a Cox model will allow estimating adjusted *P* values and hazard ratios with 95% CIs, in order to take into account confounding factors. The assumption of proportional hazards over time in the Cox model will be verified using the cumulative sum of residuals method. The functional form of the association between continuous factors and the hazard of recurrence will be assessed using the fractional polynomials method. Missing data will be imputed using a multiple imputation method adapted for survival analysis. Sensitivity analyses will examine the association between imaging and the occurrence of recurrence using different cutoffs (10%, 15%, or 20%) and by maintaining the continuous measurement through both linear and nonlinear functional forms.

### Sample size justification

2.7

The number of patients arises from comparison of the time to occurrence (censored by anticoagulation for another reason than recurrent VTE or loss to follow-up) of recurrent VTE, from the completion of anticoagulation. Based on the known recurrence risk of 4% to 7% at 1 year in patients at intermediate risk of recurrence and given that the study will also include patients with unprovoked PE whose recurrence risk is approximately 9% at 1 year, we estimated the recurrence risk in our population at 6% at 1 year (4% at 6 months and 8% at 2 years). Based on previous studies, we expect a VTE recurrence rate of 12% at 2 years in the group with RPVO (6% at 6 months) and 5% in the group without RPVO (2.5% at 6 months; hazard ratio, 2.5) [7,10,[31], [32], [33], [34]]. We anticipate that 10% of patients will be censored before 2 years (anticoagulation for another reason than recurrent VTE or loss to follow-up). We also expect that 40% of patients will have RPVO on V/Q SPECT/CT imaging, and 60% without RPVO. Thus, 52 events are required to ensure a power of 90%. Based on these assumptions, 655 patients need to be included.

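### Section 2.7: 52 events, 655 patients and 10% early censoring do not fit together; the plan's own rates give about 49 expected events and about 88–89% power

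*Protocol article*

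**What the plan says.** All the inputs are in section 2.7 of the protocol article.

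- With residual pulmonary vascular obstruction (RPVO): "we expect a VTE recurrence rate of 12% at 2 years in the group with RPVO (6% at 6 months").
- Without it: "5% in the group without RPVO (2.5% at 6 months; hazard ratio, 2.5").
- Overall recurrence risk: "6% at 1 year (4% at 6 months and 8% at 2 years").
- Group split: 40% with RPVO, 60% without.
- Early loss: "We anticipate that 10% of patients will be censored before 2 years", for anticoagulation given for another reason or loss to follow-up.

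The conclusion is "Thus, 52 events are required to ensure a power of 90%. Based on these assumptions, 655 patients need to be included". Section 2.6.2 names the test ("Kaplan–Meier curves will be compared using a log-rank test") and fixes follow-up at 2 years per patient. The article gives no alpha level, no formula, and no step that shows how the 10% enters the patient number.

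**The concern.** Getting 52 events from 655 patients means that 52/655 = 7.94% of patients have an observed event. The group rates average less than that even with complete follow-up, and the 10% early censoring can only lower the count. Yet 655 is presented as following from these assumptions, censoring included.

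The 52 events are the stated basis for 90% power. Follow-up is fixed at 2 years, and section 2.7 describes no extension until an event count is reached. If the expected count is below 52, the stated power is somewhat too favourable, and a reader cannot tell which of the printed numbers governs the study.

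**Working it through.** **Inputs.** Section 2.7: 12% and 5% at 2 years, 6% and 2.5% at 6 months, hazard ratio 2.5, 40/60 split, 10% censored before 2 years, 90% power. Assumed, because the article does not state it: two-sided alpha of 5%. One-sided 5% gives 42.5 events and does not match the plan.

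**1. The event target reproduces.** Schoenfeld's formula:

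d = (1.960 + 1.2816)² / (0.4 × 0.6 × (ln 2.5)²) = 10.508 / (0.24 × 0.8396) = 52.1.

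The hazard ratio is also consistent with the rates: ln(0.88)/ln(0.95) = 2.49.

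**2. Expected events with nobody censored.** The average 2-year risk is 0.4 × 12% + 0.6 × 5% = 7.8%, and 655 × 0.078 = 51.1. This is already just under 52.

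**3. Expected events with 10% censored evenly over 24 months.** The fraction censored by month t is 0.10 × t/24.

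- Events spread roughly evenly over follow-up (constant hazard): the average fraction still observed is about 0.95, so 51.1 × 0.95 = 48.5.
- Events front-loaded as the plan states (half by 6 months in each group): the fraction observed averages 1 − 0.10 × 3/24 = 0.9875 in the first 6 months and 1 − 0.10 × 15/24 = 0.9375 afterwards. The mean is 0.9625, so 51.1 × 0.9625 = 49.2.

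**4. Power at 655.** Schoenfeld power is Φ(√(d × 0.24 × (ln 2.5)²) − 1.960). The simulated column is a log-rank simulation with 20,000 runs per scenario.

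| Censoring | Expected events | Schoenfeld power | Simulated log-rank power |
|---|---|---|---|
| None | 51.1 | 89.4% | 89.9–90.1% |
| 10% spread over 2 years | 48.5–49.2 | 87.8–88.3% | 88.4–89.1% |
| 10% contribute no follow-up | 46.0 | 86.1% | 86.6–87.2% |

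The last row is an extreme bound, not an expectation.

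**5. Patients needed for 52 expected events.**

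- No censoring: 52/0.078 = 667.
- Censoring spread over 2 years: 52/(0.078 × 0.9625) = 693 to 52/(0.078 × 0.95) = 702.

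**6. Can 655 be recovered?** With the rounded overall risk of 8% and no allowance for censoring, 655 × 0.08 = 52.4 and 52/0.08 = 650, which is close. A Lakatos log-rank calculation that includes the 10% censoring gives 664 (front-loaded rates) to 671 (constant hazard), also close to 655, but with about 50 events. Neither route that includes the censoring gives 52 events together with 655 patients.

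**The case against.** The strongest reply is that 655 is a defensible number with the censoring included. The Lakatos results of 664–671 are only 1.3% to 2.4% above it, and the same method without censoring gives 637–638. By that method, power at 655 with the censoring is 89.3–89.6%. A reader might infer that the sponsor forgot the 10%. The article does not support that: it shows no derivation, the full protocol is not at hand, and the near match with the rounded 8% is only one possible explanation. This part of the reply stands. It does not rescue the printed pair, because the Lakatos route goes with about 50 events, not 52.

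A reader might also infer that 655 patients cannot reach 52 events. That is too strong. The count is random, and with spread-out censoring 52 or more events still occur with probability about 32–36%. What can be said is that 52 is not the expected number.

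Nor is it right to say that the study is materially underpowered. The shortfall is about 3 events, and power falls by roughly 0.5 to 2 points depending on the method. The figures of about 86–87% power, and of 741 patients (52/0.078/0.9), hold only if every censored patient contributes no follow-up. That does not fit the plan's description of patients lost or re-anticoagulated at some time before 2 years.

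Finally, a journal article may leave the formula and software to the full protocol. That excuses the missing derivation, but not printed numbers that disagree with one another.

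**Conclusion.** The concern holds as a small numerical inconsistency in section 2.7. At the plan's own rates, 655 patients are expected to give about 51 events without censoring and about 49 with the stated 10% spread over 2 years. The target is 52. Power is about 88–89% by Schoenfeld and by simulation, and up to 89.6% by Lakatos, against the stated 90%.

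This rests on a two-sided 5% alpha, which is assumed, and on censoring that is spread over follow-up and unrelated to recurrence. The cause of the mismatch is not established. The discrepancy does not threaten the design or the primary analysis, but it concerns the figures on which the study's size is justified and should be corrected.

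**What to change.** Restate section 2.7 so that its numbers agree: 655 patients, about 49 expected events, and about 88–89% power. State the alpha level and its sidedness, name the method, and say how the 10% censoring enters the calculation.

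If the sponsor prefers to keep 52 expected events, print the patient number that follows: about 693–702 with censoring spread over 2 years, that is, 38 to 47 more than 655.

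The restatement costs a sentence or two and no additional patients. Its only downside is a slightly less favourable stated power.

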### Ethics and dissemination

2.8

The study has been approved by Ouest IV Ethics Committee (ID RCB: 2023-A01566-39) and registered in ClinicalTrial.gov registry (NCT06372730). Written informed consent will be obtained from all participants. The study commenced on June 2024.

### Participant confidentiality

2.9

Any data obtained will be identified only by a participant identification number to maintain confidentiality. All records will be kept in a secured online database. If collected on paper, they will be kept in a locked cabinet. All data entry and manipulation will be performed by using participant identification numbers only.

## Discussion/Limitations of the Study

3

The major interest of the study is the potential to demonstrate that RPVO is associated with an increased risk of VTE recurrence in patients at an intermediate risk of recurrence, which is currently unknown. V/Q SPECT/CT will not be used for patients’ management and the study will not include patients on OAT, allowing an independent evaluation of the prognostic significance of RPVO for VTE recurrence.

The study also has the potential to identify predictors of recurrence other than RPVO. This may allow the identification of subgroups of patients for whom the risk of recurrence would outweigh the risk of bleeding, who would benefit from lifelong anticoagulation.

We acknowledge that this study may have some limitations.

First, while there is currently no indication to prolong anticoagulation in patients with PE provoked by a minor transient risk factor, the decision to discontinue anticoagulation in some patients with unprovoked PE includes a significant subjective component and often involves various factors such as the estimated benefit–risk balance or the patient preference. This may have a direct influence on the study population’s inherent recurrence risk and homogeneity and limit the generalizability of findings. On the other hand, it is a pragmatic approach. The population corresponds to patients for whom there is a need to better predict the risk of recurrence. Similar population heterogeneity has been observed in other studies [37]. Furthermore, the population will be well documented at inclusion. Minor risk factors associated with PE and the reasons justifying the discontinuation of anticoagulant treatment in patients with unprovoked PE (patient preference, benefit–risk balance) will be collected. Thus, subgroup analyses could be conducted. Second, as patient’s management will not be based on RPVO or other potential predictors, this noninterventional study design will not allow us to assess the impact of modifying therapeutic management based on RPVO status. Furthermore, although performing a baseline V/Q scan after 6 months of anticoagulation could present various benefits, it remains a costly examination, with unequal accessibility, and is associated with exposure to radiation. One of the secondary objectives of the study is to assess predictors of RPVO. This may allow clinicians to target patients at increased risk of RPVO, who may benefit from a baseline V/Q lung scan, and, conversely, patients with a low risk of RPVO for whom the examination would not be justified. Finally, V/Q SPECT/CT scan performed at inclusion should remain available for interpretation of any suspicion of VTE recurrence. To limit a possible bias related to the knowledge of RPVO status, all suspicions of VTE recurrence (including the suspicion confirmed and ruled out) will be adjudicated blindly by an independent central Clinical Events Committee. Furthermore, to determine RPVO status, a central review of all V/Q SPECT/CT images will be performed independently by 2 nuclear medicine physicians who will be blinded to clinical history and the patient’s outcome. Any difference in interpretation will be resolved by consensus.
